#### Secondary outcomes

Structural MRI measures will be derived from T1- and T2-weighted images to calculate cortical thickness, surface area, and subcortical volumes. Group comparisons will be conducted using ANCOVAs, controlling for sex, age, and pubertal status, with FDR correction applied across regions.

DTI data will be preprocessed with QSIPrep [98] for denoising, motion and distortion correction, followed by whole-brain tractography and structural connectome reconstruction as outlined in recent protocols [99]. Cortical parcellation will be based on the Brainnetome atlas, and structural connectivity matrices will be derived from streamline counts and weighted by fractional anisotropy. Graph-theoretical measures (e.g., node strength) will be extracted using the Brain Connectivity Toolbox. Between-group differences will be tested using ANCOVAs including sex, age or pubertal status, and medication status (yes/no) as covariates.

Task-based fMRI will be analysed using GLMs to assess BOLD activation during the stress induction task. At the first level, subject-specific GLMs will be estimated, and at the second level, group differences will be examined using ANOVAs. The primary contrast will compare stress versus baseline, with sex, age or pubertal status, and medication status (yes/no) included as covariates.

Exploratory analyses will include depressive and anxiety symptomatology scores as covariates in rsFC, sMRI, and hormonal models to test whether associations remain robust after accounting for clinical variation. Sex assigned at birth will be recorded, and exploratory analyses will examine group × sex interactions. When appropriate, non-parametric tests (e.g., Mann–Whitney U-tests) will be applied in case of non-normal distributions. Relationships between VAS ratings and hormone levels (OXT, CORT, sAA) will be assessed using bivariate correlations. Multiple regression models will also be applied to assess associations between hormonal systems. In the first model, CORT increase will be the dependent variable, with OXT increase, baseline CORT, and group as predictors. In the second model, CORT recovery will be the dependent variable, with OXT and CORT increase as predictors.

Across all analyses, effect sizes will be reported using Cohen’s d (0.2 = small, 0.5 = medium, 0.8 = large). Unless otherwise adjusted for multiple comparisons, the alpha threshold will be set at 0.05. Data will be analysed using the CONN Toolbox for neuroimaging, and IBM SPSS Statistics (Version 29.0, IBM Corp.) and jamovi (Version 2.6.22, The jamovi project, 2024) for behavioural and hormonal analyses.

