### Eligibility criteria

Eligibility is initially assessed via telephone screening and confirmed at the first study appointment. Participants must be adolescents aged 12–17 years. For the clinical groups, inclusion requires a primary diagnosis of at least moderate depression; the comorbid group additionally requires an anxiety disorder diagnosis. In case of discrepancy between clinical diagnoses and the results according to the structured clinical interview M.I.N.I.-KID, final group assignment is determined through expert consensus. Psychotropic medication and hormonal contraceptives are noted and will be corrected for but are not exclusion criteria. Full inclusion and exclusion criteria are listed in Table 1.

**Table 1 Tab1:** Inclusion and exclusion criteria

**Inclusion Criteria**	**General:** • Adolescents aged 12–17 years • Sufficient understanding of the German language • Written informed consent from participant and legal guardian
	**Depressive Group**: Primary diagnosis of depressive disorders: • Moderate depressive episode (F32.1) • Severe depressive episode without psychotic symptoms (F32.2) • Severe depressive episode with psychotic symptoms (F32.3) • Major depressive disorder, recurrent, moderate (F33.1) • Major depressive disorder, recurrent, severe without psychotic symptoms (F33.2) • Depressive disorder, recurrent, severe with psychotic symptoms (F33.3)
	**Comorbid Group**: Primary diagnosis of depressive disorders and an additional anxiety disorder: • Agoraphobia with/without panic disorder (F40.00/F40.01) • Social phobia (F40.1) • Panic disorder (F41.0) • Generalized anxiety disorder (F41.1) • Separation anxiety disorder of childhood (F93.0) • Social anxiety disorder of childhood (F93.2) • Generalized anxiety disorder of childhood (F93.80)
	**Control Group**: Matched by sex and age; school type, handedness, pubertal status, contraceptive intake are controlled for
**Exclusion Criteria**	**General**: • Pregnancy/lactation • Pubertas praecox vera • Acute suicidal behavior • Glucocorticoid-containing medication • Genetic syndromes • Traumatic brain injury • Endocrinological or immune disorders • Chronic neurological disorders affecting brain development and physiology
	**Cognitive/Developmental**: • Intellectual impairment (IQ < 80) • Attendance at a school for special needs
	**MRI-Specific**: • Metallic foreign bodies (e.g., braces, cochlear implants, non-removable piercings) • Upper-body tattoos • Claustrophobia

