	**Psychiatric Disorders**: Current/past diagnosis of: • Psychotic disorders • Autism • Bipolar disorder • Mental and behavioural disorders due to psychoactive substance use • Anorexia nervosa (if BMI < 16,5)
	**Control Group-Specific**: • Current or past psychiatric disorders • In-/outpatient psychiatric or psychotherapeutic treatment

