Social phobia is assessed using the German Screening for Social Phobia and Anxiety Inventory for Children (SPAIK) [63], based on DSM-IV criteria. The 26-item questionnaire covers psychological and physiological aspects of social phobia, with responses rated on a three-point Likert scale. The SPAIK has demonstrated strong cross-cultural validity and reliability in identifying social phobia in adolescents [64].

Anxiety symptoms are examined via the Beck Anxiety Inventory (BAI) [65, 66], a 21-item self-report scale measuring somatic and cognitive anxiety symptoms over the past seven days. The German version showed good psychometric properties, including strong convergent and divergent validity [67], and acceptable reliability in adolescent samples [68].

Depressive symptoms are assessed using the German version of the Beck Depression Inventory (BDI-II) [69, 70], a 21-item self-report scale for individuals aged 13 and older. Each item presents four statements of increasing severity, from which participants choose the one that applies most to them regarding the past two weeks. The German BDI-II shows excellent internal consistency (*α* ≥ 0.90), and reliability (>0.90), strong sensitivity to change, and good discriminative validity [71].

Dissociative states before and after neuroimaging are measured using the Dissociation-Tension Scale (DSS-4) [72], developed for repeated evaluations of state dissociation. It comprises four items (e.g., depersonalization, somatoform symptoms) rated on a 9-point Likert scale (0 = “not present”; 9 = “very strong”). The DSS-4 demonstrated good to excellent psychometric properties, including internal consistency, reliability, differential and convergent validity [72].

Participants’ current affective state during relaxation periods before and after the MRI is assessed using the German version of the Positive and Negative Affect Schedule (PANAS) [73, 74]. This 20-item self-report questionnaire comprises ten items each for positive (e.g., “enthusiastic,” “inspired”) and negative affect (e.g., “upset,” “ashamed”), rated on a 5-point Likert scale (1 = “not at all”; 5 = “extremely”). The German PANAS showed good psychometric properties [73].

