#### Primary outcomes

The first primary outcome is rsFC. We hypothesize that time (pre- vs. post-stress) × group (MDD, COM, HC) interactions will be observed in fronto-limbic connectivity.

Six a priori fronto-limbic ROIs will be examined: bilateral amygdala, hippocampus, ACC, insula, dorsolateral prefrontal cortex (dlPFC), and ventromedial prefrontal cortex (vmPFC), defined using the Harvard–Oxford cortical and subcortical atlases as implemented in the CONN toolbox [89]. This yields 15 possible pairwise connections. For each subject, mean time series will be extracted from each ROI, pairwise Pearson correlations will be computed, and coefficients will be Fisher’s z-transformed to normalize distributions. Group differences will be assessed using general linear models (GLMs) with time (pre- vs. post-stress) as within-subject factor and group (MDD, COM, HC) as between-subject factor. Sex assigned at birth, age, pubertal status (linear and quadratic terms), and medication status (yes/no) will be included as covariates. Additional psychiatric comorbidities (e.g., ADHD, OCD, PTSD, eating disorders) will be recorded but not included as routine covariates due to diagnostic heterogeneity and low subgroup frequencies; however, planned sensitivity analyses will be conducted excluding participants with additional comorbid diagnoses to assess robustness of findings. Due to the expected small number of left-handed participants, groups will not be matched on handedness; however, EHI scores will be considered as covariates in rsFC analyses. False Discovery Rate (FDR) correction across the 15 tested edges will be applied.

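### Adjusting the three-group models for depression and anxiety scores cannot test whether patient–control differences are robust, because the scores measure what separates the groups

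*Protocol article*

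**What the plan says.** In the protocol article, the exploratory paragraph under Secondary outcomes reads: "Exploratory analyses will include depressive and anxiety symptomatology scores as covariates in rsFC, sMRI, and hormonal models". The purpose follows directly: "to test whether associations remain robust after accounting for clinical variation".

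The models being extended are group comparisons. For rsFC the factors are "time (pre- vs. post-stress) as within-subject factor and group (MDD, COM, HC) as between-subject factor" (Primary outcomes). The hormonal model has a group factor crossed with time, and the structural MRI analysis is an ANCOVA between groups. Nothing limits the symptom-adjusted versions to patients.

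On group membership, Eligibility criteria say that for the clinical groups "inclusion requires a primary diagnosis of at least moderate depression; the comorbid group additionally requires an anxiety disorder diagnosis". Discrepancies between clinical diagnosis and the structured interview are resolved case by case: "final group assignment is determined through expert consensus". In Table 1 the control-specific exclusions include "Current or past psychiatric disorders". The symptom measures are BDI-II for depression and BAI for anxiety, with SPAIK for social phobia (Psychological measures).

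**The concern.** Patients are selected for being at least moderately depressed and controls for having no psychiatric history. A depression score is then close to a second copy of the patient–control variable, and an anxiety score is likely to overlap with the MDD/COM distinction. With both group and score in one model, the group term compares patients and controls at the same symptom level, where the data are thin if the scores are well separated. Severity is also part of the condition under study, so it is not an outside confounder of the patient–control difference.

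At stake is how the results are read. rsFC and hormonal reactivity are the two primary outcome domains. If a group difference found there disappears once the scores are added, the stated purpose invites the conclusion that it was not robust. That result is likely even when the difference is real.

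**Working it through.** **The plan's own figure.** Sample size and power analysis gives N = 84 (28 per group) for a one-way ANOVA with three groups, α = 0.05 and power 0.80. The effect size entered is not stated, so it was solved for. With noncentrality f²N, f = 0.35 gives N = 84 (power 0.812 at N = 84 and 0.840 at N = 90). If both patient groups differ from controls by the same d, then f = d√2/3, so f = 0.35 corresponds to d = 0.35 × 3/√2 = 0.74. The figure reproduces, and d = 0.74 serves below as a planning-size effect.

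**Assumptions, none of them from the documents.** D is the patient–control separation in depression score, in within-group SD. For rsFC, read the outcome as the pre-to-post change with the score entered as a predictor of that change.

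**Step 1: one score, none of the difference running through severity.** With patient share p = 60/90 = 2/3, the variance of the patient–control contrast is multiplied by VIF = 1 + p(1−p)D² = 1 + (2/9)D². An unadjusted power of 80% corresponds to a standardised effect of 1.96 + 0.84 = 2.80. Adjusted power is Φ(2.80/√VIF − 1.96).

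| D | VIF | 2.80/√VIF | Power |
|---|---|---|---|
| 1.5 | 1 + 0.50 = 1.5 | 2.29 | 63% |
| 2 | 1 + 0.89 = 1.9 | 2.04 | 53% |
| 3 | 1 + 2.00 = 3.0 | 1.62 | 37% |

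**Step 2: both scores, three groups.** This is a simulated single-outcome ANCOVA with 30 per group, d = 0.74, 3,000 runs per scenario and an assumed within-group correlation of 0.6 between the scores. Without the scores, power of the group test was 83–85% throughout. With both added:

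| Depression separation | Anxiety separation from HC (MDD / COM) | None via severity | Half via severity | All via severity |
|---|---|---|---|---|
| 1 | 0.5 / 1 | 74% | 28% | 5% |
| 1.5 | 1 / 1.5 | 64% | 20% | 5% |
| 2 | 1 / 2 | 55% | 16% | 6% |
| 2.5 | 1.5 / 2.5 | 45% | 14% | 5% |
| 3 | 2 / 3 | 35% | 11% | 4% |

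The adjusted patient–control estimate was 0.74–0.76 in the first case, about 0.37 in the second and about 0 in the third. In the first case its standard error rose from 0.22 to 0.25–0.41.

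**Reading.** Two mechanisms are at work. Precision falls whenever the scores separate the groups. The estimate shrinks only by the share of the difference that runs through severity. A non-significant adjusted group term can come from either one, and neither shows that the unadjusted difference was spurious.

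**The case against.** Several points on the other side stand.

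- A reader might infer that the scores define the groups. They do not. Diagnosis, the structured interview and expert consensus do, and no BDI-II or BAI cut-off assigns anyone. The overlap is likely but not definitional, and patients without an anxiety diagnosis may still score high on BAI.
- A reader might infer that real differences will be adjusted away. That is conditional. If nothing runs through severity, the estimate is kept and only precision falls; at separations of 1.5 or 2 SD the effect is still detected more often than not. Nor is overlap absent: two normal distributions 1.5, 2 or 3 SD apart share about 45%, 32% or 13% of their area.
- A reader might infer a rule by which a vanished effect discredits a primary finding. The article states a purpose and no such rule. The models are labelled exploratory, the primary models omit the scores, and structural MRI is a secondary outcome.
- That controls stay in is an inference from the three-group base models and the lack of any restriction.
- The associations to be checked may include those between hormones and rsFC, which are part of the study aim. Adjusting those for severity is defensible, and controls are informative there.
- The calculations are simplified: one outcome, with assumed separations.

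These points limit the scope and the certainty of the size. They do not rescue the check as a test of patient–control robustness, and the text does not separate that use from the defensible one.

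**Conclusion.** The point holds for the group contrasts. Followed as written, the plan yields a patient–control comparison adjusted for a near-proxy of patient status, and losing the effect there says nothing about robustness. Under assumed separations of 1.5 to 3 within-group SD, a contrast with 80% power drops to about 63% to 37% with one score and no path through severity. With both scores and half the difference running through severity, power is about 20% to 11%. These sizes depend on separations, a score correlation and severity shares that the documents do not give; the direction does not depend on their exact values. The consequence is confined to the interpretation of exploratory models and leaves the primary analyses untouched. It is worth correcting because the stated purpose bears on how both primary domains will be read.

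**What to change.** Amend the exploratory paragraph under Secondary outcomes to say three things:

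1. Symptom-adjusted group models are fitted within the two patient groups only (30 + 30 = 60), with BDI-II as covariate in the MDD versus COM comparison.
2. Anxiety score (BAI or SPAIK) is analysed as a dimensional predictor in place of the MDD/COM factor, not beside it.
3. Symptom-adjusted models will not be used to judge the robustness of patient–control differences.

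Severity adjustment of hormone–rsFC associations can stay, and should be named separately. The cost is a few sentences, with no new data or procedures. The small downside is that these exploratory group models use 60 and not 90 participants.

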### Sample size and power analysis

An a-priori power analysis was carried out with G*Power 3.1 [39]. We modelled a one-way fixed-effects Analysis of Variance (ANOVA) with three independent groups (healthy controls [HC], major depressive disorder [MDD], and MDD with comorbid anxiety [COM]).

Previous rsFC studies in adolescents with MDD report medium to large effect sizes. Connolly et al. [40] demonstrated reduced amygdala–prefrontal rsFC in adolescents with MDD compared to controls (medium effect; *d* ≈ 0.4–0.6), although numerical effect sizes were not directly reported. Cullen et al. [41] reported group differences in amygdala–prefrontal connectivity that, when derived from published means and standard deviations, correspond to large effects (*d* ≈ 1.0–1.3).

Assuming α = 0.05 (two-tailed) and a desired power of 1-*β* = 0.80, the analysis indicated a required total sample size of *N* = 84 (28 per group). To account for potential data loss due to head motion or dropout, we plan to include *N* = 90 participants, i.e. 30 per group.

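### The fallback named for non-normal data, the Mann–Whitney U-test, takes two groups and no covariates, so it cannot stand in for the adjusted three-group secondary models

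*Protocol article*

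**What the plan says.** The sentence stands in the last, largely exploratory paragraph of Secondary outcomes: "When appropriate, non-parametric tests (e.g., Mann–Whitney U-tests) will be applied in case of non-normal distributions". It names no other test, and it does not say which outcomes it covers or whether covariates are retained.

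The group comparisons described just before it are adjusted models. For structural MRI: "Group comparisons will be conducted using ANCOVAs, controlling for sex, age, and pubertal status, with FDR correction applied across regions". For DTI: "Between-group differences will be tested using ANCOVAs including sex, age or pubertal status, and medication status (yes/no) as covariates". Task fMRI uses second-level ANOVAs with the same covariate list as DTI. The number of groups is three throughout, as in the power section: "We modelled a one-way fixed-effects Analysis of Variance (ANOVA) with three independent groups".

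Two other places bear on whether adjustment matters. Under Eligibility criteria, psychotropic medication and hormonal contraceptives are allowed, with a promise to correct for them. Table 1 matches controls on sex and age, leaves pubertal status and contraceptive intake to statistical control, and excludes controls who have had psychiatric or psychotherapeutic treatment.

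**The concern.** A Mann–Whitney test asks whether the raw values of two groups come from the same distribution. The planned models ask whether three groups differ once sex, age or puberty and, in some models, medication are held fixed. The fallback changes the question, so whether an outcome is analysed with or without its confounders could depend on the shape of its distribution.

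The design makes this matter. Controls may not have had psychiatric treatment while medicated patients are eligible, so medication is likely to be unbalanced. Pubertal status is not a matching factor. An unadjusted test can then report a covariate difference as a group effect. Reading a Kruskal–Wallis test into the example restores the third group but not the adjustment.

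**Working it through.** **Inputs from the protocol article.** Three groups of 30 (Sample size and power analysis); the covariate lists (Secondary outcomes); alpha 0.05 per test unless otherwise adjusted (end of the statistical section). The plan gives no figure for this fallback, so there is none to reproduce. The required total of 84 plays no part; only the 30 per group is used.

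**Assumed inputs.** The article gives no imbalances or covariate effects. Assumed: skewed errors (gamma, shape 2, scaled to SD 1), a sex effect of 0.3, and either (a) pubertal status 0.5 SD higher in both patient groups with slope 0.5, or (b) half of patients and no controls medicated, with an effect of 0.5 SD. At least 2,000 replicates per setting, so the Monte Carlo standard error at 5% is √(0.05 × 0.95 / 2000) ≈ 0.5 percentage points.

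**Step 1: what the unadjusted test sees.** Write the outcome as y = μ + τ(group) + β·x + error. The planned null is that the three τ are equal. Under it, the raw patient–control difference is β × (mean x in patients − mean x in controls):

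- (a) 0.5 × 0.5 = 0.25 error SD
- (b) 0.5 × (0.50 − 0) = 0.25 error SD

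A rank test on raw values responds to this shift; a model containing x does not.

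**Step 2: rejection rates with no true adjusted group effect.** Kruskal–Wallis is the fair comparator, because like the ANCOVA F it is a single three-group test.

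| Setting | Kruskal–Wallis | ANCOVA with the relevant covariate |
|---|---|---|
| No imbalance | 4.7% | about 5% |
| (a) Pubertal status | 15% | 5.0–5.7% |
| (b) Medication | 17–18% | 5.2–5.4% |
| Milder (puberty 0.25 SD; or 30% medicated, effect 0.3 SD) | 6.5% to about 8% | about 5% |

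The ANCOVA holds its level despite the skew, so at this degree of non-normality the switch protects nothing.

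**Step 3: separate the pairwise problem.** With no imbalance, at least one of three uncorrected Mann–Whitney tests is significant in 11–12% (1 − 0.95³ = 14.3% if the tests were independent). Three uncorrected pairwise contrasts from the ANCOVA give 11.4–11.8%, so this excess is not peculiar to the rank test. Bonferroni-corrected Mann–Whitney gives 3.8–4.0%. In settings (a) and (b), any-pair Mann–Whitney rates of 25–32% mix this inflation with the lost adjustment.

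**Step 4: which planned models lose what.**

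- *Structural MRI* (sex, age, pubertal status): setting (a) applies. Setting (b) does not, because the planned model has no medication term and itself rejects in 15–16% there.
- *DTI and task fMRI* (sex, age or pubertal status, medication): setting (b) applies. Setting (a) applies fully only if pubertal status is the option chosen; with age instead, the adjusted model rejects in about 10% against 13% for Kruskal–Wallis.
- *Hormones* (a primary outcome; sex, age, pubertal status): no medication term, and it is unclear whether the sentence reaches them.

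**Step 5: one pair only.** If 30% of the MDD group and 60% of the comorbid group are medicated, with an effect of 0.3–0.8 SD, a single Mann–Whitney test of those two groups rejects in 6–17%, with no pairwise multiplicity involved. A rank ANCOVA holding medication gives 5–6%.

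**Step 6: power.** For a true 0.6 SD patient–control shift and a balanced covariate with slope 1.0, Kruskal–Wallis has 37–38% power, ANCOVA 64% and rank ANCOVA 65–67%. At slope 0.5 the gap nearly closes (58% against 62%).

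**The case against.** The best reply is that the sentence commits to little. It is conditional, gives Mann–Whitney only as an example, and sits beside group × sex interactions and VAS–hormone correlations, not beside the structural-MRI or DTI models. The article is condensed, and normality criteria or the exact rank procedure may properly be left to an analysis plan. This stands as a limit on reach. It does not rescue the example: the one test named fits none of the planned group comparisons.

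A reader might infer more, in four ways that the text does not support:

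- *The plan replaces all its adjusted models, including the primary ones.* It does not say so. For hormones it square-root transforms the values and keeps an adjusted model, so rank tests are not its only answer to skew.
- *The trigger is non-normality of the raw outcome.* The sentence speaks only of distributions, which could mean residuals. That needs clarifying; it is not a demonstrated error.
- *The false-positive rate is 25–32%.* That figure includes uncorrected pairwise testing, which inflates ANCOVA contrasts equally and is a separate point.
- *Lost medication adjustment affects every outcome.* The structural-MRI and hormone models never had that term.

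Matching also limits imbalance in sex and age against controls, and every imbalance simulated here is assumed.

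**Conclusion.** The point holds for the secondary group comparisons. Where a Mann–Whitney or other unadjusted rank test is used in place of an adjusted three-group model, it answers a different question and drops adjustment that the protocol promises. The cost of the lost covariate is a rejection rate of about 15–18% instead of about 5% under the assumed imbalances, and about 8% or slightly less under milder ones. The pubertal figure applies to structural MRI, and to DTI or task fMRI if pubertal status is the covariate chosen; the medication figure applies to DTI and task fMRI only. These sizes rest on assumed imbalances and effects. The mismatch between the named test and the planned models does not. It merits correction before analysis, but the documents do not show that the primary conclusions are threatened.

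**What to change.** Replace the sentence with wording such as: *Assumptions will be checked on model residuals. If these are clearly non-normal, the same three-group model and covariates are kept, with permutation (e.g., Freedman–Lane), bootstrap or HC3 inference, or a rank-transformed ANCOVA with the same covariates. Unadjusted rank tests (Kruskal–Wallis with corrected pairwise follow-up) are supplementary only.* Choose one of these as the default in advance, and state which outcomes the rule covers, including whether it reaches the primary rsFC and hormone models.

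The cost is one sentence and slightly more programming than a menu-driven rank test. No further data or participants are needed.

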## Abstract

**Background:**

Psychosocial stress is a major risk factor for adolescent depression and anxiety, impacting neurodevelopment through hypothalamic-pituitary-adrenal axis and oxytocinergic system dysregulation. Stress-related alterations in fronto-limbic resting-state functional connectivity (rsFC) have been linked to depression and anxiety disorders, yet the role of oxytocin in these processes remains unclear. Existing research often excludes comorbid anxiety or focuses on adults, limiting insights into developmental trajectories and stress-related brain changes in youth. This study aims to investigate the association of peripheral oxytocin, cortisol, and α-amylase and fronto-limbic rsFC in response to psychosocial stress in adolescents with depressive disorders, comparing those with and without comorbid anxiety disorders and healthy controls.

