In parallel, CORT—the end product of HPA axis activation—has been widely studied as a biomarker of stress-related psychopathology [27]. Evidence on OXT-CORT interactions is mixed: some human studies suggest that OXT buffers CORT reactivity [28, 29], while others report that higher stress-induced OXT is associated with increased CORT release and faster recovery [30]. Dysregulated post-stress CORT secretion, often observed in individuals with depressive and anxiety disorders [16, 31], has been associated with altered rsFC [32], particularly in circuits involved in emotional processing and self-regulation [33, 34]. In addition to CORT and OXT, salivary α-amylase (sAA), a marker of sympathetic nervous system activity [35], should be assessed simultaneously [36]. Altered sAA rhythms and reactivity have been observed in adolescents with depression and anxiety [37, 38], underscoring its relevance for understanding neuroendocrine dysregulation in these conditions.

However, little is known about how CORT interacts with OXT and sAA in shaping stress-induced rsFC changes. To our knowledge, no study has examined whether individual differences in OXT, CORT, and sAA reactivity predict fronto-limbic rsFC alterations following acute stress in adolescents with anxiety and depressive disorders.

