### Study aim

This study aims to examine associations between peripheral OXT, sAA, and CORT release, and fronto-limbic rsFC in response to psychosocial stress in adolescents with depressive and anxiety disorders, compared to healthy controls. By explicitly comparing adolescents with depression alone, comorbid anxiety, and healthy controls, this research seeks to clarify neurobiological mechanisms underlying depressive and anxiety disorders during a critical period of neurodevelopment.

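### The two secondary OXT–CORT regressions estimate only an average association across the three groups, and the CORT recovery model also leaves out group

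*Protocol article*

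**What the plan says.** The regressions stand at the end of Secondary outcomes in the protocol article. Their stated purpose is general: "Multiple regression models will also be applied to assess associations between hormonal systems". The first is set out as "In the first model, CORT increase will be the dependent variable, with OXT increase, baseline CORT, and group as predictors". The second reads "In the second model, CORT recovery will be the dependent variable, with OXT and CORT increase as predictors".

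Group is therefore a main effect in the first model and absent from the second. No product of OXT increase and group is listed, and no regression within groups is described. The one interaction named among these secondary and exploratory analyses is a different one: "exploratory analyses will examine group × sex interactions".

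Two other places matter. The Hypotheses section expects patients to show smaller CORT and OXT stress responses than controls. The Theoretical background says that the literature on the two hormones disagrees: "Evidence on OXT-CORT interactions is mixed: some human studies suggest that OXT buffers CORT reactivity", while other studies report a positive association.

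**The concern.** A group main effect only moves the intercept. With no product term, a single OXT coefficient is fitted to all three groups. That coefficient is a legitimate average, but it does not say whether patients and controls share it. A null result could hide an association confined to one group, and a significant one could be read as general when only one group carries it.

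The recovery model has a further weakness. By the study's own hypothesis, group is related to both of its predictors. If CORT recovery also differs by group for any reason not carried by CORT increase, part of that group difference passes into the OXT coefficient. The first model guards against this by adjusting for group. The second does not, and the article gives no reason for the difference.

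**Working it through.** **Inputs.** From the article: the two predictor lists, three groups of 30, and alpha 0.05. The article gives no expected OXT–CORT slope and no power figure for these regressions. Its sample size of 84, raised to 90, comes from a one-way ANOVA and does not bear on this point. All slopes and shifts below are assumptions, in standard deviation (SD) units.

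**Step 1: what the common slope estimates.** In a model with group as a main effect, the common slope is the mean of the group slopes, weighted by the within-group variation in OXT. With equal group sizes and equal OXT variance:

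b_common = (b_HC + b_MDD + b_COM) / 3

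- 0.5 in controls, 0 in both patient groups: 0.5 / 3 = 0.17.
- 0.5 in controls, 0.2 in both patient groups: 0.9 / 3 = 0.30.
- +0.4 in controls, −0.4 in both patient groups: −0.4 / 3 = −0.13. Equal and opposite slopes leave one third of the slope, with the patients' sign.
- +0.4 in controls, −0.2 in both patient groups: 0 / 3 = 0. Exact cancellation here needs a 2:1 ratio.

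**Step 2: how often each test is significant.** The table gives simulated results for the CORT increase model (3,000 to 4,000 trials per case, 30 per group, two-sided 5% level, normal errors).

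| Assumed slopes HC / MDD / COM | Average slope | Average slope significant | Patients-versus-HC slope difference (1 df) | Three-group slope difference (2 df) |
|---|---|---|---|---|
| 0.4 / 0.4 / 0.4 | 0.40 | 97% | – | 5% |
| 0.5 / 0.2 / 0.2 | 0.30 | 81% | 26% | 20% |
| 0.5 / 0 / 0 | 0.17 | 34% | 60% | 50% |
| 0.4 / −0.4 / −0.4 | −0.13 | 25% | 95% | 91% |
| 0.4 / −0.2 / −0.2 | 0.00 | 6% | 75% | 67% |
| 0.4 / 0 / −0.4 | 0.00 | 7% | – | 81% |

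The planned model works well when the slopes agree and tolerably when they differ modestly. It loses most of its power when one group alone carries the association or the signs differ. The 1-df column favours the contrast somewhat, because MDD and COM were given equal slopes in those cases.

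**Step 3: group omitted from the recovery model.** Suppose OXT has no within-group relation to recovery. Let patients be lower by δ on both OXT and CORT increase, with these two uncorrelated within groups, and lower by γ on recovery beyond what CORT increase explains. The patient indicator has variance v = (1/3)(2/3) = 0.222. The omitted-variable formula then gives a spurious OXT slope of

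γδv / (1 + 2δ²v)

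- δ = γ = 0.5: 0.0556 / 1.111 = 0.05.
- δ = γ = 0.8: 0.1422 / 1.284 = 0.11.
- γ = 0: no bias, whatever δ is.

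In simulation with shifts of 0.5 to 0.8, the recovery model as written finds a false OXT effect in roughly 8% to 18% of trials. With group added, the rate returns to about 5%. A positive within-group correlation ρ between the two increases adds ρ to the denominator and so reduces the bias.

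**The case against.** The strongest reply is that the models do what they were set to do. Their stated purpose is to assess the association between hormonal systems, and an average slope adjusted for group answers that. Group differences in the size of the hormone response are tested by the repeated-measures ANOVAs among the primary outcomes. This stands for the CORT increase model: its common slope is a valid summary and should stay.

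Three stronger readings are tempting, and the article does not support them.

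- A reader might infer that the study aim requires a group comparison of the OXT–CORT slope. The aim does compare groups, "in response to psychosocial stress in adolescents with depressive and anxiety disorders, compared to healthy controls", but the association it names is between hormone release and fronto-limbic connectivity. No hypothesis predicts that the OXT–CORT slope differs by group.
- A reader might infer from the mixed literature that the slope reverses with diagnosis. The Theoretical background says only that studies disagree. It does not tie the sign to patient status.
- A reader might infer that opposite slopes would cancel to a finding of no association. With two patient groups and one control group they generally do not. The zero averages in the table come from values that force zero.

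It is also fair to say that power for modest slope differences is low, and that checks of equal slopes are often left to a fuller plan. But the article does list the predictors of both models, and the reply does not explain why group is in one and missing from the other.

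**Conclusion.** The point holds in a limited form. Both regressions estimate an average OXT association and cannot show whether it differs between MDD, COM and HC. Dilution can be large: the average slope is significant in 34% of trials when only controls have a slope of 0.5, and in 25% when slopes are +0.4 in controls and −0.4 in patients. Under a common slope of 0.4 the planned CORT increase model has 97% power, so its average is not wrong in itself.

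The missing group term in the recovery model is the firmer defect. It can produce a spurious OXT effect, but only if recovery also differs by group beyond what CORT increase explains. That condition is plausible, but the article does not state it.

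Every slope and shift used here is an assumption. The analyses are secondary, and no primary outcome, sample size or stated hypothesis rests on them. This is an inexpensive improvement to make before analysis.

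**What to change.** 1. Add group as a main effect to the CORT recovery model, as in the CORT increase model.
2. Keep the common OXT slope in both models and describe it as the average association across the three groups.
3. As a labelled exploratory analysis, add OXT increase × group to both models and report the OXT slope with its 95% confidence interval in each group.
4. Do not state that the average holds in every group unless the group-specific estimates support it.

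No new data are needed. Group costs two degrees of freedom in the recovery model, and the interaction costs two more in each model. Intervals for slope differences will be wide at 30 per group. The 2-df interaction in the CORT increase model reaches 80% power only at a partial R² of about 0.10 with 90 participants, and a 0.5 versus 0.2 difference between controls and patients would be detected in only about 26% of trials even with the 1-df contrast. A non-significant interaction should therefore not be taken as evidence that the slopes are equal.
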